#### Sample size

2.1.2

The sample size estimation for this study was calculated based on the results of a pilot study by Cairns (2018). This pilot study was selected as a reference for several reasons: both studies involve similar populations (family members of ICU patients), comparable intervention intensity (continuous intervention over 3 days, each lasting 15–20 min), similar assessment tools and outcome indicators (key indicators in this study were selected from those that performed well in the Cairns’ study, or alternative validated tools were chosen to address its limitations), and largely aligned assessment time points (the Cairns’ study assessed on Day 1, Day 3, Day 30, and Day 90; this study additionally included an assessment within 24 h after patient discharge to better reflect the interaction between patients and their families). In the pilot study (*N* = 10; 5 per group), the effect size for the outcome of perceived stress from baseline to 90-day follow-up was Cohen’s *d* = 1.13 (95% CI: −0.21 to 2.47), based on a mean difference of 4.4 points (intervention: 23.0 ± 2.30 vs. control: 25.0 ± 5.05). This effect size represented the most conservative estimate among all follow-up time points (Day 3: *d* = 1.50; Day 30: *d* = 1.23; Day 90: *d* = 1.13). Sample size estimation for the “independent sample *t*-test” was performed in G Power3.1 sample size calculation software,^1^ and the calculation formula is as follows: 
$n={\left[\frac{Z_{\alpha /2}+Z_{\beta }}{\delta /\sigma }\right]}^{2}(Q_{1}^{-1}+Q_{2}^{-1})$
 (Faul et al., 2007; Faul et al., 2009). The parameter Settings are as follows: For the two-sided test, Cohen’s d is 1.13, Alpha is 0.05, the certainty Power (1-β) is 0.95, and the sample size is selected as N1 = N2. Finally, it was calculated that each group of the intervention study required 22 people. Considering a loss to follow-up rate of more than 20%, the minimum sample size included in each group was ultimately 28 people. When the sample size was sufficient, as many research subjects as possible were included in the study. Acknowledging the inherent variability and potential overestimation in pilot studies, we aimed for a conservative design by selecting a high statistical power to minimize the risk of Type *II* error.

To account for the inherent uncertainty in the pilot-derived effect size estimate, we conducted a sensitivity analysis using a range of more conservative effect sizes. The results are shown in Table 1. With 28 participants per group, our trial maintains 80% power to detect a medium-to-large effect (*d* = 0.7), which we consider a clinically meaningful target.

**Table 1 tab1:** Sensitivity analysis of sample size under different effect size scenarios.

Scenario	Effect size (d)	Power	Required N per group	Our *N* = 28 achieved power
Pilot estimate (Day 90)	1.13	0.95	20	>99%
Large effect	0.80	0.95	36	88%
Medium-large effect	0.70	0.95	46	80%
Medium effect	0.50	0.80	64	51%
Lower bound of 95% CI	0.21	0.80	358	12%

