**Methods:**

This study will recruit 56 family members of ICU patients from a hospital in China. Participants will be randomly assigned to either the experimental group or the control group. The control group will receive standard care, and the experimental group will receive standard care plus a stress management intervention. The primary outcome is a composite score of psychological distress (integrating perceived stress, anxiety, and depression) measured immediately post-intervention. Secondary outcomes include the longitudinal trajectories of individual psychological symptoms (stress, anxiety, depression), symptoms of post-traumatic stress, and sleep quality across multiple follow-ups up to 90 days. Data analysis will be performed utilizing IBM SPSS version 27.0 software.

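### The planning effect d = 1.13 conflicts with the pilot means printed beside it and is not for the Day 3 composite, so 95% power is not established for the primary endpoint

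*Protocol article*

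**What the plan says.** Section 2.1.2 (Sample size) bases the calculation on one pilot study: "In the pilot study (*N* = 10; 5 per group"). The planning value is described this way: "the effect size for the outcome of perceived stress from baseline to 90-day follow-up was Cohen’s *d* = 1.13 (95% CI: −0.21 to 2.47"). The same sentence gives its source: "based on a mean difference of 4.4 points (intervention: 23.0 ± 2.30 vs. control: 25.0 ± 5.05"). The section ranks the pilot effects by time point as "Day 3: *d* = 1.50; Day 30: *d* = 1.23; Day 90: *d* = 1.13" and treats the last as the most cautious. The value then enters an independent-samples t-test calculation: "For the two-sided test, Cohen’s d is 1.13, Alpha is 0.05, the certainty Power (1-β) is 0.95, and the sample size is selected as N1" (that is, two equal groups). The result is 22 per group, raised to 28 for loss to follow-up. The section closes by saying that "we aimed for a conservative design by selecting a high statistical power".

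The primary endpoint is a different quantity. The Abstract states: "The primary outcome is a composite score of psychological distress (integrating perceived stress, anxiety, and depression) measured immediately post-intervention". Section 2.6 (Statistical analysis) builds this composite as the sum of z-scores on PSS-10, GAD-7 and PHQ-9 at Day 3 and analyses it by ANCOVA with the baseline composite as covariate.

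**The concern.** Two things do not fit. First, the mean difference said to underlie d = 1.13 is more than twice the difference between the two means in the same bracket. Second, the effect belongs to one construct at Day 90, while the trial will be judged on a three-scale composite at Day 3, and no effect on that composite is given.

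The base-case calculation of 22 and then 28 per group uses this d and nothing else. If the input is wrong, or is for a different quantity, the 95% power attached to it does not describe the primary comparison. A reader of a null result could then wrongly take it as coming from a trial with 95% power for its primary endpoint. Choosing a high nominal power does not help: it limits the type II error at the assumed d and gives no protection if that d is overstated.

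**Working it through.** **Inputs, all from section 2.1.2:** means 23.0 and 25.0; SDs 2.30 and 5.05; 5 per group; stated difference 4.4; stated d = 1.13 with 95% CI −0.21 to 2.47; two-sided alpha 0.05; power 0.95; 1:1 allocation.

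**1. From d to N (reproduces).** A two-sample t test with d = 1.13 and power 0.95 needs 21.4, so 22 per group. With 20% loss, 22/0.8 = 27.5, so 28. This step is sound.

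**2. From the stated difference to d (reproduces closely).**
- Pooled SD = √[(2.30² + 5.05²)/2] = √[(5.29 + 25.50)/2] = 3.92.
- 4.4/3.92 = 1.12, close to 1.13.
- SE of d = √(2/5 + 1.13²/20) = 0.681, so the interval is 1.13 ± 1.96 × 0.681 = −0.20 to 2.46, close to the one stated.

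So 1.13 and its interval come from the 4.4.

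**3. From the printed means to d (does not reproduce).**
- 25.0 − 23.0 = 2.0.
- 2.0/3.92 = 0.51, with approximate 95% CI −0.75 to 1.77.
- Other denominators do not recover 1.13: 2.0/5.05 = 0.40 and 2.0/2.30 = 0.87.

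**4. What the fixed N can detect.** For an unadjusted t test, two-sided 0.05, 80% power:
- 28 per group: d = 0.76.
- 22 per group (the full loss allowance used up): d = 0.86.

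Under ANCOVA with baseline correlation r, the detectable effect is multiplied by √(1 − r²). With 28 per group it becomes 0.73, 0.66 or 0.54 for r = 0.3, 0.5 or 0.7. These correlations are assumptions; section 2.1.2 states none.

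**5. Conditional illustration, if d were 0.51 with 28 per group.**
- Unadjusted t test: about 47% power.
- ANCOVA, using d/√(1 − r²): about 50%, 58% or 75% for r = 0.3, 0.5 or 0.7.

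**6. Endpoint comparison.**

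| | Sample size calculation | Primary analysis |
|---|---|---|
| Outcome | perceived stress (pilot scale not named) | sum of PSS-10, GAD-7 and PHQ-9 z-scores |
| Time | baseline to Day 90 | Day 3 |
| Method | independent-samples t test | ANCOVA on baseline composite |

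**The case against.** The strongest reply is that the 4.4, the d of 1.13 and the confidence interval agree with one another, so the two means may be the odd ones out. The phrase "the effect size for the outcome of perceived stress from baseline to 90-day follow-up" suggests a change from baseline, and 4.4 could be a between-group difference in change printed beside end-point means. This stands: a reader might infer that the pilot effect was really 0.51 and that the trial has only 47% power, and the article does not support that. It does not clear the passage, though. If 4.4 is a change-score difference, the text does not say so, and dividing it by the SDs attached to 23.0 and 25.0 uses the SD of other scores.

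A second reply is that the uncertainty is already disclosed. The section concedes that pilots may overestimate effects, and Table 1 covers effects down to d = 0.21, printing 51% power at d = 0.50 with 28 per group. The text beside it names d = 0.7 as a meaningful target. This also stands in part: the risk from smaller effects is not hidden. But the base case stays at d = 1.13 with 95% power, and nothing in the table is tied to the composite.

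Third, the pilot's Day 3 effect on stress (1.50) exceeds the Day 90 one, and ANCOVA can raise power. So the choice is cautious as to time point, and unadjusted power figures may be too low for the planned analysis. Neither point supplies an effect for the anxiety and depression components, or a baseline correlation.

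Finally, the 22-per-group figure is a lower bound on information. The primary endpoint falls at Day 3, the primary analysis imputes missing values, and the Limitations section places the attrition risk in the 90-day follow-up.

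**Conclusion.** The point holds in this form. Section 2.1.2 contradicts itself on the figure that drives the base-case sample size: the printed means differ by 2.0 (d = 0.51) against a stated 4.4 (d = 1.12). Which figure is wrong cannot be settled from the article. Separately, the planning effect is for perceived stress at Day 90, so the stated 95% power is not established for the Day 3 composite.

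The arithmetic from d = 1.13 to 22 and 28 per group is correct; only the input is in doubt. It would go too far to say that the trial is shown to be underpowered. The 47% figure assumes both d = 0.51 and an unadjusted test, and under ANCOVA with assumed baseline correlations of 0.3 to 0.7 it becomes about 50% to 75%. What can be said without the pilot is the detectable effect: d = 0.76 with 28 per group at 80% power, unadjusted, and smaller if a baseline correlation is justified.

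**What to change.** 1. Check the pilot source and reconcile the bracket. Either correct the means or the 4.4, or label 4.4 as a difference in change and give the change-score means and change-score SDs behind it. Recompute d and its interval, and name the pilot's stress scale.
2. Restate the justification for the primary endpoint as the effect on the Day 3 composite detectable with the fixed N at 80% power, two-sided 0.05: d = 0.76 with 28 per group, or about 0.86 if only 22 per group are analysed (unadjusted t test). If an ANCOVA gain is claimed, state the assumed baseline correlation and the resulting figure.
3. Do not present 95% power as a property of the primary endpoint, and remove the claim that high power makes the design conservative against an overstated pilot effect.

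The cost is a check of the pilot report and a rewording of section 2.1.2. The stated power becomes less favourable. The sample size, the endpoint and the analysis stay as they are.

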. Finally, the three standardized scores will be summed to obtain the participant’s psychological distress composite score: 
$\text{CompositeScor}e_{i}=Z_{i,\mathrm{PSS}-10}+Z_{i,\mathrm{GAD}-7}+Z_{i,\mathrm{PHQ}-9}.$
 (2) Primary statistical model. The primary between-group comparison at Day 3 will be performed using an analysis of covariance (ANCOVA), with the Day 3 composite score as the dependent variable, experimental group as the fixed factor, and the baseline composite score as a covariate. Prior to ANCOVA, normality of residuals and homogeneity of regression slopes will be assessed. If the assumptions of ANCOVA are violated, a non-parametric alternative (e.g., Quade’s rank ANCOVA) will be applied. (3) Effect size and validation. To assess the clinical significance of the intervention effect, Cohen’s d effect size will be calculated, with *d* = 0.2 considered a small effect, *d* = 0.5 a medium effect, and *d* = 0.8 a large effect (Bartko et al., 1988). As a validation step, the theoretical standard deviation of the composite score will be computed using the variance sum theorem: 
$SD_{\text{theoretical}}=\sqrt{3+2(r_{12}+r_{13}+r_{23})}$
. where 
$r_{12}$
, 
$r_{13}$
, and 
$r_{23}$
 represent the Pearson correlation coefficients between each pair of the three scales. This theoretical value will be compared with the observed standard deviation to confirm the construct validity of the composite score. (4) Sensitivity analyses. As a sensitivity analysis, a per-protocol (PP) analysis will be conducted to evaluate the robustness of the primary ITT results. Additionally, to assess the potential impact of contamination, we will perform an analysis excluding control group participants who received protocol-prohibited psychological support during the intervention window.

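### The claim of 80% power at d = 0.7 and several cells of Table 1 have no valid stated basis: the named t-test gives 73%, and the planned ANCOVA reaches 80% only with an unstated correlation of about 0.40

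*Protocol article*

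**What the plan says.** In the Protocol article, the Sample size section (2.1.2) gives the planning method: "Sample size estimation for the “independent sample *t*-test” was performed in G Power3.1 sample size calculation software". The settings are: "For the two-sided test, Cohen’s d is 1.13, Alpha is 0.05, the certainty Power (1-β) is 0.95", with equal groups ("the sample size is selected as N1 = N2"). The result is that "each group of the intervention study required 22 people", and then: "Considering a loss to follow-up rate of more than 20%, the minimum sample size included in each group was ultimately 28 people".

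The same section adds a sensitivity table (Table 1) with five effect sizes. For each it gives a required number per group and the power reached with 28 per group. The text draws one conclusion from the table: with 28 per group "our trial maintains 80% power to detect a medium-to-large effect", specified as d = 0.7. Neither the table nor the text around it names the test behind these figures.

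The Statistical analysis section (2.6) fixes the primary test: "The primary between-group comparison at Day 3 will be performed using an analysis of covariance (ANCOVA"), with the baseline composite score as covariate. No correlation between baseline and Day 3 scores is given.

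**The concern.** Two tests could lie behind the power figures: the t-test named for the sample size and the ANCOVA named for the primary analysis. A power statement needs one of them and its inputs. The t-test inputs are all printed, so the claim can be checked directly. The ANCOVA also needs the baseline to Day 3 correlation, which is absent.

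The d = 0.7 sentence matters because it is how the plan defends itself against an overestimated pilot effect. If the primary result is null, readers will judge it against that 80%. A printed figure above what the stated method delivers makes the trial look more informative at its own target effect than it has been shown to be.

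**Working it through.** **Inputs.** Two-sided alpha 0.05, equal groups, d = 1.13 and power 0.95 for the main calculation, and the d values and target powers of Table 1, all from Sample size. The ANCOVA model is from Statistical analysis. The correlation ρ between baseline and Day 3 composite is not given, so it is assumed over 0 to 0.7.

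**Formulas.**
- t-test: noncentrality λ = d·√(n/2), with 2n − 2 degrees of freedom. Power is the probability that a noncentral t exceeds the two-sided 5% critical value in absolute size.
- ANCOVA with one covariate: the same, with d replaced by d/√(1 − ρ²) and 2n − 3 degrees of freedom.

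**Step 1: the plan's main figure.** The printed normal-approximation formula gives 2 × ((1.960 + 1.645)/1.13)² = 20.4, so 21. The exact noncentral t calculation gives 22, with power 95.6%. Allowing for 20% loss, 22/0.8 = 27.5, so 28. The 22 and the 28 both reproduce. Table 1 prints 20 for the same d and the same power, which contradicts the text.

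**Step 2: the d = 0.7 claim under the t-test.** λ = 0.7 × √14 = 2.619 with 54 degrees of freedom and critical value 2.005. Power is 73.0%, against the printed 80%.

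**Step 3: the whole table.** ρ = 0.4 is shown because it fits the d = 0.7 row.

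| d (target power) | Required n: printed | t-test | ANCOVA, ρ = 0.4 | Power at 28: printed | t-test | ANCOVA, ρ = 0.4 |
|---|---|---|---|---|---|---|
| 1.13 (0.95) | 20 | 22 | 19 | >99% | 98.6% | 99.5% |
| 0.80 (0.95) | 36 | 42 | 36 | 88% | 83.6% | 89.4% |
| 0.70 (0.95) | 46 | 55 | 46 | 80% | 73.0% | 80.1% |
| 0.50 (0.80) | 64 | 64 | 54 | 51% | 45.1% | 51.8% |
| 0.21 (0.80) | 358 | 357 | 300 | 12% | 12% | 13% |

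The t-test fits the required n in the last two rows (to within one participant) and the 12%. It misses the other cells, though in the first row only narrowly. An ANCOVA with ρ of about 0.38 to 0.40 fits 36, 46, 80% and 51%, but cannot give 64 or 358. Solving for ρ from the printed powers gives 0.35 for 88%, 0.40 for 80% and 0.38 for 51%. No single basis reproduces the table.

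**Step 4: the d = 0.7 power under the planned ANCOVA.**

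| ρ (assumed) | 28 per group | 22 per group |
|---|---|---|
| 0 | 73% | 62% |
| 0.3 | 77% | 66% |
| 0.4 | 80% | 70% |
| 0.5 | 84% | 74% |
| 0.7 | 95% | 89% |

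Reaching 80% needs ρ of at least 0.397 with 28 per group, or 0.588 with 22.

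**Step 5: is t-test sizing a problem for the ANCOVA?** At d = 1.13 and 95% power, the ANCOVA needs 22 per group at ρ = 0, 20 at 0.3, 17 at 0.5 and 12 at 0.7. The extra degree of freedom costs about 0.1 percentage point or less. The t-test figure is therefore a practical floor.

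**The case against.** The strongest defence is that planning on an unadjusted t-test and analysing by ANCOVA is common, accepted and conservative in a randomised trial. Baseline adjustment shrinks residual variance by the factor 1 − ρ², so power can in practice only rise. Two assessments a couple of days apart may well correlate at 0.4 or more, in which case the trial would have its 80%. The sample size is unaffected, and a condensed article need not print every planning input.

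Much of this stands. A reader might infer from the t-test and ANCOVA mismatch that no stated power applies to the primary analysis, or that the sample size must be redone. The document does not support either reading: the 22 and 28 at d = 1.13 reproduce and are conservative for the ANCOVA. Nor can Table 1 simply be called a t-test table, since the article does not say so and several cells disagree with one. The fit of other cells to ρ near 0.4 may be coincidence.

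The defence does not rescue the 80%, because the floor at d = 0.7 is 73% and the printed figure lies above it. A plausible but unstated correlation is not a stated basis, and it would still leave 64 and 358 unexplained.

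The 22-per-group column should not be pressed. The loss allowance carries no time point, the Limitations section places attrition in the 90-day follow-up, and the Day 3 endpoint is analysed by intention to treat with multiple imputation. It is a low-end case, not the expected one.

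**Conclusion.** The power statement at d = 0.7 and several cells of Table 1 are wrong as written for the only test that the sample size section names. The overstatement of power at 28 per group is 7 percentage points at d = 0.7, about 4 at d = 0.8 and about 6 at d = 0.5. Required numbers for 95% power are understated by 2, 6 and 9 per group at d = 1.13, 0.8 and 0.7. The t-test results rest only on printed inputs. The ANCOVA results rest on an assumed ρ, a linear baseline relation, and d expressed in unadjusted standard deviations.

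The choice of a t-test for sizing is not a fault, and the main calculation holds arithmetically for d = 1.13. Whether 1.13 is a sound effect size for this endpoint is a separate question and is not judged here.

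**What to change.** Keep 56 participants and the ANCOVA.

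- Recompute every row of Table 1 with the stated two-sided t-test. Required n becomes 22, 42, 55, 64 and 357. Power at 28 per group becomes 98.6%, 83.6%, 73.0%, 45.1% and 12%.
- Name that test in the table title, and say that the figures are a lower bound for the ANCOVA.
- Restate power at d = 0.7 with 28 per group as about 73%.
- If a higher figure is wanted, give it as ANCOVA power beside its assumed correlation and a range: 77%, 80%, 84% and 95% at ρ = 0.3, 0.4, 0.5 and 0.7.
- Optionally, show 22 per group (62% by t-test) as a low-end case.

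The cost is a corrected table and one reworded sentence. No participants are added and the analysis does not change. The lower-bound version needs no new assumption. Only the optional ANCOVA figures need a correlation that the authors must defend.

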### Statistical analysis

2.6

In this study, EpiData3.1 software will be utilized for data entry, while IBM SPSS Statistics version 27.0 will be employed for data analysis.

All statistical tests were two-sided with *α* = 0.05, and *p* < 0.05 indicated significance. Categorical variables, including family member demographics, will be presented as counts and percentages and compared between groups using the *chi-square* test or *Fisher’s* exact test, as appropriate. Continuous variables will be assessed for normality using the *Shapiro–Wilk* test. Normally distributed data will be summarized as mean ± standard deviation, while non-normally distributed data will be summarized as median and interquartile range. For baseline comparisons of continuous variables, independent samples *t*-tests or *Mann–Whitney U* tests will be applied accordingly. For the intention-to-treat (ITT) analysis, missing data from participants who withdraw during the study will be handled using multiple imputation (MI). Specifically, the multiple imputation module in SPSS version 27.0 will be employed to create five complete datasets using the fully conditional specification method, with group allocation, time point, baseline scores, and demographic characteristics included as predictor variables. The imputed results will then be pooled for analysis.

Primary Outcome Analysis: The primary analysis will follow the ITT principle, including all randomized participants. The efficacy of the SAF-T intervention will be assessed by comparing the psychological distress composite score at the primary endpoint (Day 3) between the intervention and control groups, adjusting for the baseline composite score. (1) Calculation of the composite score. To ensure comparability across time points, all composite scores will be standardized using the means and standard deviations calculated from the Day 3 assessments. For each participant at Day 3, the composite score will be calculated as follows: First, for each of the three scales (PSS-10, GAD-7, and PHQ-9) administered at Day 3, the mean (
${\overset{ˉ}{x}}_{k}$
) and standard deviation (
$SD_{k}$
) will be calculated across all participants, where 
k=1,2,3
 represents the three scales, respectively. Second, for each participant 
i
, the raw score on each scale (
$x_{\mathrm{ik}}$
) will be standardized to a Z-score: 
$Z_{\mathrm{ik}}=\frac{x_{\mathrm{ik}}-{\overset{-}{x}}_{k}}{SD_{k}}$

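### Table 1 understates the required sample size at d = 1.13, 0.80 and 0.70 (20, 36 and 46 per group should be 22, 42 and 55), and its first row contradicts the 22 on which the trial is sized

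*Protocol article*

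**What the plan says.** Section 2.1.2 (Sample size) gives the settings in full. The calculation "was performed in G Power3.1 sample size calculation software" for an independent-samples t-test with equal groups. It is specified as follows: "For the two-sided test", Cohen's d of 1.13, "Alpha is 0.05, the certainty Power (1-β) is 0.95". The result is that "each group of the intervention study required 22 people", raised to 28 for losses above 20%. A normal-approximation formula is printed beside this. Section 2.6 confirms the sidedness: "All statistical tests were two-sided with" alpha 0.05.

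Table 1, in the same section, then varies the effect size. Its column "Required N per group" reads:

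- d = 1.13, power 0.95: 20
- d = 0.80, power 0.95: 36
- d = 0.70, power 0.95: 46
- d = 0.50, power 0.80: 64
- d = 0.21, power 0.80: 358

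No other test, sidedness, alpha or covariate correlation is given for the table.

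**The concern.** The text and the first row of Table 1 use the same d and the same power but give different answers, 22 and 20. The second and third rows also look too small for a two-sided t-test at 95% power.

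The table carries weight because the pilot effect comes from 10 people, with a 95% confidence interval from −0.21 to 2.47. It is there to show how far 28 per group falls short if that effect is inflated. If the column is too low at d = 0.80 and d = 0.70, it understates the shortfall at the effects the sponsor labels large and clinically meaningful.

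**Working it through.** **Inputs**, all from section 2.1.2 and Table 1: two-sample t-test, two-sided, alpha 0.05, 1:1 allocation, with d and power as printed in each row.

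**Method.** With n per group, power is the probability that a non-central t variable with 2n − 2 degrees of freedom and non-centrality d·√(n/2) falls outside ± the 97.5% point of the central t. The required n is the smallest that reaches the target. This is the exact calculation for the stated test.

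**Step 1: reproduce the sponsor's figure.** For d = 1.13 and power 0.95, the smallest n is 22. Non-centrality is 1.13 × √11 = 3.75 and power is 95.6%. Allowing for 20% loss, 22 / 0.80 = 27.5, which rounds up to 28. The text's 22 and 28 are both correct.

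**Step 2: the same calculation for every row.**

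| d | Target power | Printed n | Exact t | Normal approximation | Power at printed n |
|---|---|---|---|---|---|
| 1.13 | 0.95 | 20 | 22 | 21 | 93.6% |
| 0.80 | 0.95 | 36 | 42 | 41 | 91.7% |
| 0.70 | 0.95 | 46 | 55 | 54 | 91.3% |
| 0.50 | 0.80 | 64 | 64 | 63 | 80.1% |
| 0.21 | 0.80 | 358 | 357 | 356 | 80.1% |

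The last two rows reproduce, to within one person. The first three do not.

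**Step 3: the printed formula.** With Q1 = Q2 = 0.5, the bracket of reciprocals equals 4, so the formula gives total N. At 95% power, (1.960 + 1.645)² = 12.995, and the results are:

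- d = 1.13: 12.995 / 1.13² × 4 = 40.7 in total, or 20.35 per group
- d = 0.80: 12.995 / 0.64 × 2 = 40.61 per group
- d = 0.70: 12.995 / 0.49 × 2 = 53.04 per group

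Rounded up, these are 21, 41 and 54. The printed 20 is 20.35 rounded down, and the formula cannot give 36 or 46.

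**Step 4: could one unstated method explain the column?** Printed values, in row order: 20, 36, 46, 64, 358.

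- One-sided t-test: 18, 35, 45, 51, 282. This also contradicts the stated two-sided test.
- Baseline-adjusted variance (factor 1 − ρ²) with ρ = 0.4: 19, 36, 46, 54, 300. Rows 2 and 3 match; rows 1, 4 and 5 do not.
- Power 0.90 instead of 0.95 in rows 1 to 3: 18, 34, 44.

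None of these reproduces all five rows.

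**Step 5: size.** At d = 0.80 the shortfall is 42 − 36 = 6 per group (6/42 = 14%). At d = 0.70 it is 55 − 46 = 9 per group (9/55 = 16%). In total numbers, row 3 implies 2 × 46 = 92 analysed participants, whereas 2 × 55 = 110 are needed.

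**The case against.** The arithmetic cannot reasonably be disputed. The case on the other side concerns weight and remedy.

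- **Enrolment does not depend on the column.** The 28 per group comes from d = 1.13 and the correct 22. This stands.
- **The shortfall is already visible.** The printed 36 and 46 both exceed 28, so the table already shows that 95% power is not reached at these effects. Correction enlarges a disclosed gap and reverses no conclusion. This also stands, but the table exists to show the size of that gap.
- **Row 1 is a small discrepancy.** It is 2 per group and looks like a mix of methods plus rounding down. That is fair, but identical inputs still have two printed answers, and 20 does not deliver the 95% shown in its own row.
- **The comparison of 110 with 56 needs care.** The text claims 80% power, not 95%, at d = 0.70, and 110 counts analysed participants while 56 counts enrolled ones. The figure is a fair check of row 3, which prints 0.95. It should not be read as the shortfall against the sponsor's 80% claim.
- **A baseline correlation may lie behind rows 2 and 3.** The primary analysis in section 2.6 is a baseline-adjusted ANCOVA, and ρ = 0.4 gives exactly 36 and 46. With ρ of about 0.35 to 0.40, 28 per group also gives powers close to the adjacent column's 88%, 80% and 51%. This is plausible but remains conjecture: no correlation is stated, section 2.1.2 names a plain t-test, and rows 1, 4 and 5 do not fit. If true, the table mixes two methods without saying so, which is itself a fault.

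**Conclusion.** The point holds for the first three rows of the required-N column. Under the test stated in section 2.1.2, the entries 20, 36 and 46 should be 22, 42 and 55. The understatement is 2, 6 and 9 per group, and at the printed sizes power is 93.6%, 91.7% and 91.3% rather than 95%. Row 1 also contradicts the sizing calculation in the text. The d = 0.50 and d = 0.21 rows are acceptable.

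The conclusion rests only on inputs the article prints: two-sided t-test, alpha 0.05, equal groups, and the d and power of each row. The normal approximation, at 21, 41 and 54, leads to the same judgement. The planned 28 per group is unaffected. What is wrong is the sensitivity evidence offered in its support, and in all three rows the error runs in the reassuring direction.

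**What to change.** In Table 1, replace 20, 36 and 46 with 22, 42 and 55, and state that every row uses the two-sided independent-samples t-test in G*Power. Remove the normal-approximation formula, or say that it gives total N and was not the method used. If the sponsor did assume a baseline correlation for some rows, state its value and source and apply it to all five rows; the corrected entries would then differ from those above.

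Recalculate the achieved-power column by the same method at the same time, so that the rows do not mix methods. Under the plain t-test, 28 per group gives 83.6% at d = 0.80 (printed 88%), 73.0% at d = 0.70 (printed 80%) and 45.1% at d = 0.50 (printed 51%). The sentence after the table's introduction that claims 80% power at d = 0.7 depends on that column and would need the same check.

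The cost is a correction to one table and its surrounding text. Recruitment target, design and analysis do not change.

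### Table 1 overstates achieved power: at d = 0.7 an unadjusted t-test gives about 73% with all 28 per group and about 62% with the 22 left after the planned loss, not 80%

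*Protocol article*

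**What the plan says.** All of this is in the Protocol article, section 2.1.2 (Sample size), including Table 1.

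- Method: "Sample size estimation for the “independent sample *t*-test” was performed in G Power3.1 sample size calculation software".
- Inputs, with equal group sizes: "For the two-sided test, Cohen’s d is 1.13, Alpha is 0.05, the certainty Power (1-β) is 0.95, and the sample size is selected as N1".
- Result: "it was calculated that each group of the intervention study required 22 people".
- Allowance for loss: "Considering a loss to follow-up rate of more than 20%, the minimum sample size included in each group was ultimately 28 people".
- Answer to possible pilot overestimation: "we aimed for a conservative design by selecting a high statistical power to minimize the risk of Type" II error.
- Robustness: "we conducted a sensitivity analysis using a range of more conservative effect sizes". The last column of Table 1 is headed "Our *N* = 28 achieved power" and reads >99%, 88%, 80%, 51% and 12% for d = 1.13, 0.80, 0.70, 0.50 and 0.21.
- Summary: "With 28 participants per group, our trial maintains 80% power to detect a medium-to-large effect" (d = 0.7), which the authors regard as clinically meaningful.

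Section 2.3.1 sets the primary endpoint at Day 3. Section 2.6 analyses all randomized participants by ANCOVA on the baseline composite, with multiple imputation for missing Day 3 outcomes. Section 3.1 discusses attrition over the 90-day follow-up, chiefly after discharge.

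**The concern.** The text and the table use different numbers for the same trial. The text treats six of the 28 per group as people the trial can afford to lose. The table counts those six as contributing full information when it asks how the design performs at smaller effects. Its power values are also higher than 28 per group can give under the stated test.

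The column is the plan's only evidence that the trial remains useful if the pilot estimate (10 participants in total) was too large. A reader who accepts 80% at d = 0.7 will put the chance of missing that effect at 20%. If the true figure lies between 27% and 38%, a null result is weaker evidence against d = 0.7 than the article implies.

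**Working it through.** **Inputs (section 2.1.2).** Two-sided α = 0.05, 1:1 allocation, independent-samples t-test, d = 1.13 with power 0.95 for the sizing, 22 analysed and 28 enrolled per group.

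**Formula.** Power is the probability that a noncentral t variable with 2n − 2 degrees of freedom and noncentrality d·√(n/2) exceeds the two-sided critical value in absolute size. This is the standard calculation for the test named.

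**Step 1: the enrolment figure reproduces.** d = 1.13 at 95% power gives n = 21.4, so 22 per group. Then 22/(1 − 0.20) = 27.5, so 28. The allowance is 28 − 22 = 6 per group.

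**Step 2: the achieved-power column.** At d = 0.7 the noncentrality is 0.7·√14 = 2.62 for n = 28 (54 df) and 0.7·√11 = 2.32 for n = 22 (42 df). All rows:

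| d | Table 1 | n = 28, no loss | n = 22, planned loss |
|---|---|---|---|
| 1.13 | >99% | 98.6% | 95.5% |
| 0.80 | 88% | 83.6% | 73.6% |
| 0.70 | 80% | 73.0% | 62.1% |
| 0.50 | 51% | 45.1% | 36.7% |
| 0.21 | 12% | 12.1% | 10.5% |

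The last row reproduces at 28 and the first is only slightly high. The three middle rows do not reproduce. At d = 0.7 the normal approximation gives 74.5% and a one-sided test 82.7%, so neither variant explains 80%. The two-sided t-test needs 33 to 34 per group for 80% at d = 0.7.

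**Step 3: splitting the gap.** At d = 0.7 the total is 80 − 62.1 = 17.9 points. Of this, 80 − 73.0 = 7.0 is error in the column at 28, and 73.0 − 62.1 = 10.9 comes from ignoring the planned loss. At d = 0.8 the split is 4.4 and 10.0 points; at d = 0.5 it is 5.9 and 8.4.

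**Step 4: dependence on loss by Day 3.** At d = 0.7, a loss of 0, 5, 10, 15 and 20% of 28 gives power of 73.0, 70.7, 68.3, 65.7 and 62.9%. The last uses n = 22.4; at exactly 22 it is 62.1%.

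**Step 5: smallest effect with 80% power.** d = 0.76 at 28 per group and d = 0.86 at 22.

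**Step 6: what the 95% setting bought.** At d = 1.13, 80% power needs 13.3, so 14 per group. Choosing 95% added 22 − 14 = 8 analysed per group, before any dropout allowance.

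**The case against.** **Baseline adjustment.** The primary analysis is ANCOVA, so an unadjusted t-test understates its power. This stands as a caveat. At d = 0.7, baseline correlations of 0.3, 0.4, 0.5 and 0.6 give 66, 70, 75 and 81% at 22 per group; at 28 per group, 0.3, 0.4 and 0.5 give 77, 80 and 84%. A correlation near 0.38 would bring the three middle power values within 2 points of Table 1. It would also give required numbers of 35.7 and 46.4 at d = 0.8 and 0.7, where the table has 36 and 46. It does not fit the rest of the table: at d = 0.5 and 0.21 it would need 55 and 306 per group, whereas the table shows 64 and 358, close to the unadjusted 64 and 357. The plan states no correlation and names a t-test. Even at 0.38, power at d = 0.7 with 22 per group is about 69%.

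**Timing of loss.** The primary endpoint is Day 3, and the attrition discussed is mostly later. This also stands: no Day 3 loss rate is given, so 22 is the low end under the plan's own allowance, not a forecast. Zero loss still gives only 73%.

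**Multiple imputation.** All 28 remain in the analysis set, but imputation does not restore the information in outcomes that were never observed.

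**The sentence on conservatism.** A reader might infer that the whole claimed margin against pilot overestimation is the dropout allowance used twice. The document does not support that. The sentence rests on the 95% setting, which is already inside the 22 and gives a real margin from d = 1.13 to 0.86. Only the further step from 0.86 to 0.76 uses the allowance. Nor does the plan claim 95% power at d = 0.7: Table 1 puts that requirement at 46 per group and openly shows 80% for 28.

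**Conclusion.** The point holds for Table 1 and the 80% statement beside it. Under the unadjusted two-sided t-test that the plan names, power at d = 0.7 is about 73% with no loss and about 62% after the planned loss. No loss rate yields 80% without a baseline adjustment that the plan does not quantify. The risk of missing that effect is therefore 27% to 38%, against the 20% implied.

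Two stronger conclusions are tempting and should be resisted. Dropout does not explain the whole gap: about 7 of the 18 points at d = 0.7 are error in the column at 28. And power of 62% to 73% weakens a null result but does not make it uninformative.

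The sentence on conservatism is overstated, not false. With 22 analysed, the high power setting protects down to about d = 0.86, which falls short of the 0.7 that the authors regard as clinically meaningful.

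**What to change.** 1. Recompute the achieved-power column of Table 1 and show it at both 28 (no loss) and 22 (planned 20% loss) per group. The existing values for 28 need correcting; adding a column for 22 is not enough.
2. Replace the 80% statement with wording such as: *At d = 0.7 power is about 73% with no loss and about 62% after 20% loss (unadjusted t-test); 80% power holds at d = 0.76 and d = 0.86 respectively.*
3. Add that loss by Day 3 may be below 20%, and that ANCOVA would raise power by an amount depending on the baseline correlation. If a correlation is assumed, state it and show a range.
4. Reword, rather than delete, the sentence on conservatism: 95% power at d = 1.13 with 22 analysed gives 80% power down to about d = 0.86, which does not reach the d = 0.7 target.

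The cost is one table column, a few sentences and a less favourable stated power. Enrolment does not need to change.
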